### Participant recruitment and group allocation

2.4

Eligible patients will be identified and recruited by clinicians within the Department of Respiratory and Critical Care Medicine at Shijiazhuang People’s Hospital. Research nurses will provide prospective participants with comprehensive information regarding the study. Given the inherent nature of the intervention—which necessitates active patient engagement with technology—strict randomization may compromise adherence and ecological validity. Therefore, following the provision of written informed consent, participants will be allocated to either the IoT-assisted PR group or the conventional PR group based on their initial preference and a preliminary assessment of technology readiness and digital competency (e.g., smartphone ownership, basic digital literacy). This pragmatic allocation approach is designed to reflect real-world implementation conditions. Participants who initially prefer conventional care but express willingness to engage with IoT technology will be encouraged to join the IoT-assisted PR group to maximize recruitment efficiency. Baseline characteristics of both groups will be rigorously compared and statistically adjusted in all subsequent analyses. We acknowledge that an attention-matched control group is not feasible in this pragmatic study design due to resource constraints and the inherent nature of the IoT intervention. This limitation will be discussed more clearly in the Discussion section.

### Interventions

2.5

Figure 2 illustrates the pulmonary rehabilitation pathway in this study.

**Figure 2 fig2:**
[figure not shown]
Standard pulmonary rehabilitation pathway. The conventional pulmonary rehabilitation group (control group) will receive physician interface assessment and therapist interface execution in hospital; the IoT-enhanced pulmonary rehabilitation group (intervention group) will receive a comprehensive IoT-based rehabilitation management, in addition to physician interface assessment and therapist interface execution in hospital.

#### Conventional pulmonary rehabilitation group (control group)

2.5.1

Participants will receive standard care consistent with GOLD guidelines, comprising the following components:

##### In-hospital education

2.5.1.1

A structured educational program delivered by nurses and physiotherapists, covering COPD pathophysiology, pharmacological management (including inhaler technique), energy conservation strategies, nutritional guidance, and smoking cessation counseling.

##### Standardized home-based PR prescription at discharge

2.5.1.2

Participants will receive verbal and written instructions for home-based PR, including:

Breathing exercises: pursed-lip breathing and diaphragmatic breathing, 15 min per session, twice daily.Resistance training: upper limb strengthening exercises using standardized resistance bands (e.g., lateral arm raises at 40–50% of one-repetition maximum), three sets of ten repetitions per day.

##### Follow-up assessments

2.5.1.3

Outpatient clinic visits will be scheduled at 1, 3, 6 and 12 months for clinical evaluation, spirometry, and questionnaire administration. No remote monitoring or proactive feedback regarding PR adherence will be provided during the follow-up period.

#### IoT-enhanced pulmonary rehabilitation group (intervention group)

2.5.2

In addition to standard education and the initial PR prescription, participants in this group will receive a comprehensive IoT-based management model. The system architecture of IoT-based platform is illustrated in Figure 3.

IoT platform and devices: participants will be provided with an IoT-enabled threshold-load respiratory training device and a dedicated smartphone application (“Breathing Tribe,” patient-facing interface). A clinician portal and therapist application will facilitate remote management. A pulse oximeter will be provided to ensure exercise safety monitoring.Individualized prescription delivery via the platform: at discharge, clinicians will use the portal to generate personalized, dynamic PR prescriptions based on baseline assessment findings (e.g., 6MWT results, MIP), which will be electronically transmitted to the patient’s application. The prescription will encompass:

Respiratory muscle training (RMT): twice daily using the IoT device. Initial intensity will be set at 30% of MIP, with weekly increments of 5%, up to a maximum of 60% MIP. The device will automatically record training frequency, duration, and achieved inspiratory/expiratory pressures.Aerobic and resistance training: home-based walking prescribed at 50–60% of the average speed achieved during the 6MWT, combined with resistance band exercises (identical protocol to the control group). The application will provide instructional videos and a built-in timer.Medication and nutritional management: the application will incorporate medication reminders and deliver personalized dietary recommendations based on Nutritional Risk Screening 2002 (NRS2002) assessment results.

**Figure 3 fig3:**
[figure not shown]
Architecture of the IoT-based pulmonary rehabilitation management platform, illustrating the closed-loop interaction among patients, devices, and the clinical team.

The following specifications are added to the intervention protocol

Exact training duration: each RMT session will last approximately 15–20 min. Each aerobic training session (walking) will last 20–30 min per session, with resistance training lasting an additional 10–15 min.Target weekly exercise time: total target weekly exercise time is 150–180 min, distributed as 3–5 sessions per week (approximately 30–50 min per session).Progression rules for walking training: based on patient-reported tolerance and the absence of adverse events, advancement is carried out after three consecutive training sessions have been completed. Each increase is 5 min, until reaching 30–45 min. Then the intensity is adjusted, with walking speed increased by approximately 0.5 km/h each time. At least two weeks of observation are required after each adjustment. If tolerated, the target walking speed will be increased from 50–60% of the average speed on the 6-min walk test to 60–70% after 4 weeks.Progression rules for resistance training: when participants can comfortably complete 2 sets of 12 repetitions each, the number of repetitions for the resistance band training will be increased, up to a maximum of 15 repetitions. After 2 weeks of observation, if there are no adverse reactions, the intensity (differentiated by color-coded resistance levels) will be increased to the next resistance level, maintaining the same repetition target. Once both the number of repetitions and the resistance level have been successfully increased, the number of sets will be increased from 2 sets to 3 sets. The increase in the number of sets must only be carried out after the intensity and number of repetitions have been stabilized.Stopping criteria during exercise: participants will be instructed to stop exercise immediately if they experience chest pain, severe dyspnea (mMRC ≥ 3), dizziness, palpitations, or intolerable fatigue.Safety thresholds for SpO₂ or symptoms: exercise will be paused if SpO₂ drops below 88% or falls by ≥4% from baseline resting saturation. Exercise may resume when SpO₂ returns to ≥90% and symptoms resolve. If SpO₂ remains below 88% after two minutes of rest, the session should be terminated and the clinician notified. For symptoms, exercise will be stopped if Borg dyspnea score ≥ 5 or Borg fatigue score ≥ 5 (on 0–10 scale).

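### The IoT group's resistance prescription contradicts itself, and for a resting SpO₂ of 94% or more one reading can meet both the pause rule and the oxygen part of the resume rule

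*Protocol article*

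**What the plan says.** **Resistance training.** Section 2.5.1.2 prescribes control participants resistance-band work at "three sets of ten repetitions per day". Section 2.5.2 says the IoT group receives the initial prescription too, and lists "resistance band exercises (identical protocol to the control group" among its components. The specifications printed after Figure 3 then give a progression. It is triggered "when participants can comfortably complete 2 sets of 12 repetitions each", raises repetitions to at most 15, then moves up one band level, and only after that goes from 2 sets to 3. On frequency, "total target weekly exercise time is 150–180 min, distributed as 3–5 sessions per week". The Abstract also puts aerobic and resistance exercise at 3–5 sessions a week.

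**Oxygen saturation.** In the same specifications, "exercise will be paused if SpO₂ drops below 88% or falls by ≥4% from baseline resting saturation". Then: "Exercise may resume when SpO₂ returns to ≥90% and symptoms resolve". And: "If SpO₂ remains below 88% after two minutes of rest, the session should be terminated and the clinician notified".

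**Related statements.** Exercise stops at once for severe dyspnea, given as mMRC 3 or more, and separately at a Borg dyspnea or fatigue score of 5 or more. Section 3.1.2 uses mMRC as the dyspnea outcome. A session is about 30–50 min. Its parts are walking of 20–30 min plus resistance work of 10–15 min, and walking later progresses to 30–45 min. Section 3.1.2 defines the training completion rate, for the intervention group, as days with the prescribed rehabilitation completed divided by prescribed training days.

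**The concern.** Resistance work appears in both arms. If it is the same in both, it is background treatment. If the IoT group follows its own sets, repetitions, frequency and progression, it is part of the difference being tested. The text supports both readings, so a reader of the results could not say what was compared. The frequency conflict also reaches an outcome, because the completion rate needs a count of prescribed days.

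The saturation rules are meant for unsupervised exercise at home. A pause rule that refers to the participant's own baseline, paired with a resume rule that does not, can give opposite instructions on the same reading.

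**Working it through.** **1. Resistance prescription, side by side**

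| | Section 2.5.1.2 (control; called identical in 2.5.2) | Specifications after Figure 3 (IoT) |
|---|---|---|
| Sets | 3 | 2, rising to 3 as the last step |
| Repetitions per set | 10 | 12 at the progression trigger, up to 15 |
| Frequency | daily | 3–5 sessions a week |

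Repetitions per week, counting one exercise and reading daily as seven days:
- Control: 3 × 10 × 7 = 210.
- IoT at the progression trigger: 2 × 12 = 24 per session; 24 × 3 = 72 to 24 × 5 = 120.
- IoT fully progressed: 3 × 15 = 45 per session; 45 × 3 = 135 to 45 × 5 = 225.

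These counts ignore load. They show only that the two descriptions are not one protocol.

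Effect on the completion rate: take an IoT participant who does everything else prescribed, and resistance work in every one of 3 weekly sessions. If resistance work is prescribed only on session days, all 7 days of the week count as completed (7/7 = 100%). If it is prescribed daily, only 3 do (3/7 = 43%). With 5 sessions the daily reading gives 5/7 = 71%.

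**2. SpO₂ pause and resume**

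Let B be the resting value and S the reading.
- Pause: S < 88, or B − S ≥ 4.
- Oxygen part of resume: S ≥ 90.
- Both hold when 90 ≤ S ≤ B − 4, which requires B ≥ 94.

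| Resting SpO₂ | Readings meeting both |
|---|---|
| 93% or less | none |
| 94% | 90% |
| 96% | 90–92% |
| 98% | 90–94% |

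Reading the 4% as a relative fall (S ≤ 0.96 × B) gives the same whole-number readings: 0.96 × 93 = 89.3 (none), 0.96 × 94 = 90.2 (90%), 0.96 × 98 = 94.1 (90–94%).

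**3. mMRC as an in-exercise stop**

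Neither the inclusion nor the exclusion criteria (Sections 2.2.1 and 2.2.2) refer to mMRC, so a participant graded 3 or 4 at baseline can enrol. Read literally, that participant meets the stop criterion before starting.

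**4. Weekly minutes**

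The stated target is 150–180 min. With the stated sessions of 30–50 min it can be reproduced: 5 × 30 = 150, 3 × 50 = 150, and 4 sessions of 37.5–45 min give 150–180. With the listed components:

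| Sessions | Initial, (20 + 10) to (30 + 15) = 30–45 min | After walking progression, (30 + 10) to (45 + 15) = 40–60 min |
|---|---|---|
| 3 | 90–135 | 120–180 |
| 4 | 120–180 | 160–240 |
| 5 | 150–225 | 200–300 |

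Three initial sessions cannot reach 150 min, and five progressed sessions always exceed 180 min. The other four cells overlap the target. Respiratory muscle training is left out: twice daily at 15–20 min, it takes 14 × 15 = 210 to 14 × 20 = 280 min a week by itself.

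**The case against.** The prescription is individualized and adjusted through the platform, so the ranges need not multiply out, and no single dose has to fit everyone. The word identical might mean the same type of exercise at the start, with progression added for the IoT group. Resumption also requires symptoms to have resolved, so the oxygen overlap is not by itself permission to continue.

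Much of this stands. A reader might infer more than the text supports:
- *That sessions times minutes contradict the weekly target.* They do not. The target is reachable at 3, 4 and 5 sessions of the stated length. Only the component durations fall short or overshoot, and only in the two cases shown.
- *That a reading of 88–89% after rest falls into a gap.* It does not. That participant has not met the resume condition and stays paused.
- *That mMRC and Borg are rival stop rules.* They are additive triggers, and either can stop exercise.
- *That the conflict in minutes undermines the completion rate.* The rate counts days, so minutes do not enter it.
- *That the automated alerts act on conflicting rules.* Section 3 has them fire when values fall below predefined thresholds, and nothing shows that the resume rule drives them.

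Individualization does not rescue the resistance text. A participant who starts on the control prescription is already at three sets, whereas the progression starts from two and makes the third set its final step. Nor does the symptom condition rescue the saturation rules, because a fall in SpO₂ can pause a participant who has no symptoms.

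**Conclusion.** Two contradictions hold on the text.

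The IoT resistance prescription is stated in two incompatible ways, on sets, repetitions and frequency. This leaves open whether resistance work differs between the arms. In the worked case, the completion figure for the same behaviour is 100% or 43%, depending on the reading. That illustration assumes every other prescribed element is done.

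For a resting SpO₂ of 94% or more, every reading from 90% up to baseline minus 4 meets the pause rule and the oxygen part of the resume rule. A symptom-free participant therefore meets both in full. At a resting value of 93% or less there is no overlap. The document does not give the distribution of resting SpO₂, so the number affected is unknown.

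The mMRC stop and the component durations are minor. The number of participants with baseline mMRC of 3 or more is also not given, and the progressed minutes assume that resistance time stays at 10–15 min. None of this touches the sample size or the primary outcome definition. It bears on home-exercise safety, on what the comparison tests, and on one adherence measure.

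**What to change.** Before enrolment, the investigators should reconcile:
- Section 2.5.1.2, Section 2.5.2 and the specifications after Figure 3 on the resistance prescription in each group, stating whether it is meant to be common to both arms;
- the SpO₂ pause and resume statements;
- the use of mMRC, an outcome scale, as a stop during exercise;
- the component durations against the weekly target, at the start and after progression.

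Prescribed training days in Section 3.1.2 should then be counted against the reconciled prescription. Which dose, threshold or stopping rule applies is for the clinical team, and none is proposed here. The cost is protocol wording and matching app settings. No procedure, visit or measurement is added.

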#### Inclusion criteria

2.2.1

Age between 40 and 75 years.A confirmed diagnosis of COPD according to GOLD criteria, defined as a post-bronchodilator FEV₁/FVC ratio < 0.70 and FEV₁ % predicted < 80% (GOLD grades 2–4) at enrollment.A history of at least two moderate acute exacerbations or one severe acute exacerbation requiring hospitalization within the preceding 12 months (Group E according to the GOLD guideline).Clinical stability for a minimum of four weeks prior to enrollment, defined as the absence of acute exacerbations or changes in pharmacological regimen.Capacity to provide written informed consent and willingness to comply with all study procedures, including utilization of IoT devices and the smartphone application.

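### The SpO₂ pause, resume and terminate rules are not consistent: at resting values of 94% or more some readings meet both pause and resume, and 88–89% after rest has no stated end point

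*Protocol article*

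**What the plan says.** The rules stand in the specifications added to the intervention in section 2.5.2 of the protocol article, after Figure 3, in the item on safety thresholds. Three consecutive sentences govern SpO₂:

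- Pause: "exercise will be paused if SpO₂ drops below 88% or falls by ≥4% from baseline resting saturation".
- Resume: "Exercise may resume when SpO₂ returns to ≥90% and symptoms resolve".
- Terminate: "If SpO₂ remains below 88% after two minutes of rest, the session should be terminated and the clinician notified".

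The same item adds a separate symptom stop at a Borg dyspnea or fatigue score of 5 or more. The item before it lists symptoms at which exercise must stop.

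Section 3 (remote monitoring, feedback and dynamic prescription adjustment) says that the therapist receives an automated alert when parameters such as SpO₂ fall below thresholds fixed in advance. It does not give those thresholds.

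The inclusion criteria in section 2.2.1 define severity by spirometry, "FEV₁ % predicted < 80% (GOLD grades 2–4) at enrollment". Neither they nor the exclusion criteria list a limit on resting SpO₂.

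**The concern.** One of the two pause triggers is measured from the participant's own resting value, while the single resume condition is a fixed level. Two rules on different scales can overlap, so that one reading both demands a pause and permits exercise. The resume and terminate rules also have different cut-offs, which leaves a band between them.

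Participants in the intervention group apply these rules during exercise at home, and safety is one of the study's stated objectives (Introduction, third objective). If the rules can be followed in more than one way, a participant, a therapist and the app may act differently on the same reading. Exercise exposure and the recorded safety events could then depend on who interprets the rule.

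**Working it through.** The plan gives no figure to reproduce. The check runs the three sentences over whole-percent readings.

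**Inputs** (all from the safety thresholds in section 2.5.2), with R the resting SpO₂ and S the current reading:

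- Pause if S < 88 or R − S ≥ 4.
- Resume allowed if S ≥ 90 and symptoms have resolved.
- Terminate and notify if S < 88 after two minutes of rest.

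**Step 1: overlap of pause and resume.** The relative trigger holds when S ≤ R − 4, and the SpO₂ part of the resume rule when S ≥ 90. Both hold when 90 ≤ S ≤ R − 4. That range contains a reading only if R − 4 ≥ 90, that is R ≥ 94.

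| Resting SpO₂ (%) | First reading that triggers a pause (%) | Readings that meet both pause and resume (%) |
|---|---|---|
| 92 | 88 | none |
| 93 | 89 | none |
| 94 | 90 | 90 |
| 95 | 91 | 90–91 |
| 96 | 92 | 90–92 |
| 97 | 93 | 90–93 |
| 98 | 94 | 90–94 |

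A participant without symptoms and with a reading in the last column is told to pause and allowed to resume on that same reading. On resuming, R − S is still at least 4, so the pause rule is met again.

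**Step 2: does the meaning of the 4% matter?** Read as a relative fall, the trigger is S ≤ 0.96 × R. At R = 94 this is 0.96 × 94 = 90.24, so the first whole-percent trigger is 90. At R = 93 it is 0.96 × 93 = 89.28, so the first trigger is 89. The cut-off at a resting value of 94% is the same either way.

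**Step 3: the other reading of the resume sentence.** The sentence speaks of SpO₂ returning to 90%, which could be taken to cover only falls below that level. Then a participant paused at, say, 92% from a resting 96% has no resume rule at all. Neither reading makes the sentences fit.

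**Step 4: after two minutes of rest.**

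| Reading after rest (%) | Rule that applies |
|---|---|
| 87 or less | terminate and notify |
| 88 or 89 | neither resume nor terminate |
| 90 or more | may resume if symptoms have resolved |

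The rules themselves can put a participant in the middle row: at resting values of 92% and 93% the relative trigger first fires at 88% and 89%. A pause from a lower reading can also recover only as far as that band.

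**The case against.** The strongest defence is that the sentences can be applied sensibly together. Resumption is permissive and presupposes recovery, and the pause trigger is never suspended. A band between resume and terminate is a hold that keeps the participant at rest, which is no contradiction. Clinicians may also hear of a low reading through the alerts in section 3. Much of this stands, and it rules out several stronger readings.

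- A reader might infer that the relative trigger does nothing at resting values of 94% or more, or that it matters only at 92–93%. It does not follow. At a resting 95% and a reading of 89%, the 88% trigger is silent, the relative trigger pauses exercise, and resumption must wait for 90%. The relative trigger acts at readings of 88–89% for resting values of 93% or more, and at 88% for a resting 92%.
- A reader might infer that someone resting at 97% may keep exercising down to 90%. The pause rule is met again at any reading of 93% or below, so the text does not authorise that.
- A reader might infer that no instruction applies at 88–89% after rest. The participant remains paused. What is missing is an end point for the hold.
- A reader might infer that no clinician would learn of such a reading. That is not established, because section 3 describes SpO₂ alerts at levels the article does not give.
- Redundancy of the relative trigger at resting values of 90–91%, where it would fire at 86–87%, is ordinary for two triggers joined by an or.

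The defence does not remove the overlap. The resume sentence sets no condition tied to the resting value, so in the range found in step 1 the text gives two answers to one reading. The symptom and Borg stops act independently and do not address a fall in SpO₂ without symptoms. Nor is this detail left out when a full protocol is condensed: the article prints exact thresholds, and those thresholds do not fit together.

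**Conclusion.** The point holds in a limited form. For a participant without symptoms and with a resting SpO₂ of 94% or more, readings from 90% to the resting value minus 4 meet both the pause rule and the resume rule. If the resume sentence is confined to falls below 90%, the pause in that range has no resume rule. At 88–89% after two minutes of rest the participant is held with no stated end point and no notification under this rule.

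The 94% cut-off follows from the printed thresholds for whole-percent readings and needs no outside assumption. How many participants are affected cannot be stated, because the article gives no distribution of resting SpO₂. The point concerns safety conduct in the intervention group. It does not touch the sample size, the error rate or the primary analysis. Any effect on exposure or on recorded safety events is possible, but the article does not allow it to be quantified.

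**What to change.** The clinical and safety team should reconcile the pause, resume and terminate sentences in section 2.5.2 with one another and with the SpO₂ alert thresholds mentioned in section 3. After the change:

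- each pause trigger should have a resume condition that matches it;
- every reading after the rest period should lead to one stated action, including whether the clinician is notified.

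The values are for that team, and none is proposed here. The cost is wording in the protocol, the app instructions and the patient instructions. No change to the design, the sample size or the analysis is needed.
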